#### Criteria for discontinuing or modifying allocated interventions

Subjects can leave the study at any time for any reason if they wish to do so without any consequences. The investigator can decide to withdraw a subject from the study for urgent medical reasons. There will be no follow-up of patients who withdraw from the study, but reasons for withdrawal will be recorded. Patients who withdraw from the study will not be replaced.

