### Sample size

Our primary outcome is the between-group difference in overall knee pain 12 weeks after PT and 18 weeks after TTT and PT, measured with the VAS score. Our hypothesis is that the improvement in the TTT group will be greater than the improvement in the PT group.

To detect the superiority of the treat-to-target TTT with PT to PT alone, we calculated the required sample size for an independent samples t-test on the following assumptions: power (1-beta) 0.8, significance level (alpha) 0.05, and two-sided testing. Effect size was set at the MCID for VAS-pain, based on a study by Crossley et al., who demonstrated that a change in the VAS score of two points or more is considered clinically relevant and worthwhile for performing surgery [28]. Based on a study by Bayoumi et al., which compared different surgical techniques for patellar maltracking without instability, the anticipated mean for the PT only group was 6.2 (reflecting the pre-operative value), and SD was 2.0 [17]. Based on these parameters, a sample size of 16 patients per group is needed. Anticipating on a loss to follow-up of 20%, 20 patients per group are needed.

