### Statistical methods for primary and secondary outcomes

In accordance with the iPFRN, the REPORT-PFP consensus statement outcome measure description will be adequate [35]. The items described in the assessment will be in adequate detail to allow replication. We will report *n* (%), the mean (SD), and median (interquartile range; IQR) for categorical/descriptive, normally distributed continuous and non-normally distributed continuous data, respectively [35]. Results over time will be visualized descriptively in spaghetti plots. The primary analyses will be performed following the intention-to-treat method.

Statistical analyses will be done using *R* software (R Foundation for Statistical Computing, Vienna, Austria).

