#### Methods for additional analyses (e.g., subgroup analyses)

Per-protocol analyses will be performed including only the patients that did not crossover from the PT to TTT group, for comparison with intention-to treat analysis.

Methods in analysis to handle protocol non-adherence and any statistical methods to handle missing data.

Patient adherence to the PT will be extracted from the weekly questionnaire and will be reported. To test whether this affects the primary outcome, adherence will be added as extra covariate in the multivariable linear regression analysis as sub analysis.

In the case of missing outcome values, data will be imputed before analysis using multiple imputation methods.

Plans to provide access to the full protocol, participant-level data and statistical code.

The trial protocol provided to the METC is available from the corresponding author upon reasonable request. Data will be handled according to the FAIR principles (a guideline to improve the Findability, Accessibility, Interoperability, and Reusability of Digital Assets) [37]. After completion of the study, metadata will be available upon request. For access to anonymised participant-level data and statistical code, an application can be submitted to the corresponding author.

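### Follow-up stops for everyone who withdraws, with no exception for investigator withdrawals or patients still willing to answer questionnaires, which risks avoidable missing outcome and safety data

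*Protocol article*

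**What the plan says.** The rule is in the Protocol article, under Criteria for discontinuing or modifying allocated interventions. Patients may go at will: "Subjects can leave the study at any time for any reason if they wish to do so without any consequences". The investigator may also act: "The investigator can decide to withdraw a subject from the study for urgent medical reasons". The next sentence is "There will be no follow-up of patients who withdraw from the study, but reasons for withdrawal will be recorded", followed by "Patients who withdraw from the study will not be replaced". Despite its heading, the section describes only departure from the study. It does not describe stopping treatment while remaining under observation.

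The analysis sections then say "The primary analyses will be performed following the intention-to-treat method" (Statistical methods for primary and secondary outcomes) and "In the case of missing outcome values, data will be imputed before analysis using multiple imputation methods" (Methods for additional analyses). The sample size section allows for 20% loss to follow-up.

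Other sections keep some patients in data collection whatever treatment they receive. Under TTT and PT versus PT only, crossover patients continue surveys and measurements. Under Physiotherapy (PT) programme, non-compliance leads to a conversation with the physiotherapist, not to removal. Under Methods for additional analyses, adherence enters a sub-analysis as a covariate, which presupposes that poor adherers still supply outcomes.

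**The concern.** An intention-to-treat analysis protects the randomised comparison to the extent that outcomes are sought from everyone randomised. Here the primary outcome is the VAS at week 12 (PT arm) or week 18 (TTT arm). A patient who withdraws before that point therefore has no primary outcome, by rule and not by refusal.

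An urgent medical reason is plausibly related to both pain and treatment, and only the TTT arm starts with surgery and a splint phase. In the PT arm, the Discussion itself foresees some patients losing motivation for physiotherapy. Loss could therefore be related to outcome and could differ between arms.

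Safety is affected too. Adverse events are recorded to week 12 or 18, but a patient withdrawn during that window leaves follow-up under this rule.

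This is a data-collection rule, so an analysis plan cannot undo it: scores that were never collected can only be modelled.

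**Working it through.** **Reproducing the plan's own figure.** The inputs in Sample size are "power (1-beta) 0.8, significance level (alpha) 0.05, and two-sided testing", a difference of 2 cm (the plan's stated basis is that "a change in the VAS score of two points or more is considered clinically relevant and worthwhile for performing surgery") and an SD of 2.0.

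- Normal approximation: n = 2 × (1.96 + 0.84)² × (2.0/2)² = 15.7, so 16 per group. This matches the plan.
- Allowance for loss: 16 / (1 − 0.20) = 20 per group. This matches too.
- The exact t-test gives 16.7, so 17 per group. Its power is 78.1% at 16 and 86.9% at 20 per group. The one-patient gap is immaterial here.

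The 20% allowance protects precision. It does not protect against bias if those who leave differ from those who stay.

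**Size of the possible bias.** Suppose k of 20 patients in one arm have no outcome, and their true mean pain is d cm worse than the imputed mean.

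- True arm mean = [(20 − k) × observed mean + k × (imputed mean + d)] / 20
- Estimated arm mean = [(20 − k) × observed mean + k × imputed mean] / 20
- Shift = k × d / 20

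The documents give no value for d; 1 to 3 cm is an assumption.

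| Lost in one arm (k) | d = 1 cm | d = 2 cm | d = 3 cm | Share of 2 cm |
|---|---|---|---|---|
| 1 of 20 (5%) | 0.05 | 0.10 | 0.15 | 2.5% to 7.5% |
| 2 of 20 (10%) | 0.10 | 0.20 | 0.30 | 5% to 15% |
| 4 of 20 (20%) | 0.20 | 0.40 | 0.60 | 10% to 30% |

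The last row takes the whole planned loss as informative and confined to one arm, so an apparent 2.0 cm difference would really be 1.8, 1.6 or 1.4 cm if that arm were TTT.

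**Direction.** Losing poor performers from TTT overstates its benefit; losing them from PT understates it. With the same d in both arms, the net bias is d × (k in TTT − k in PT) / 20, which is zero when the losses are equal.

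**Likely number of surgical cases.** The article puts all major complications of TTT below 1%. Among 20 operated patients that is fewer than 20 × 0.01 = 0.2 expected. Major complications alone would therefore seldom produce even one such withdrawal. Other medical reasons, and patients who leave but remain willing to answer, come on top; the article gives no rate for either.

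**The case against.** The case against has real force on several points.

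- **Stopping treatment is not the same as withdrawing.** A reader might infer that anyone who stops or departs from the allocated treatment is lost. The documents do not support that: crossover patients and poor adherers to PT stay in data collection.
- **Some loss is unavoidable.** A patient who refuses all contact cannot be followed under any wording. The avoidable part is investigator withdrawal and those who leave but would still answer.
- **Coverage of investigator withdrawals is a reading.** The rule speaks of patients who withdraw. Because it directly follows the sentence on investigator withdrawal and carries no exception, that reading is reasonable, but it is not spelled out.
- **Complications have their own reporting route.** They are handled as adverse events, asked about at visits and reported. That helps up to the moment of withdrawal, not after it.
- **Imputation is not useless.** Baseline VAS, the 6-week questionnaire and the weekly VAS during PT could absorb part of the bias for someone who leaves during PT. They help less for someone who leaves before PT starts. The imputation model and any sensitivity analysis may be in an analysis plan that is not shown, so their absence is no criticism.
- **The article is a condensation.** The full protocol may separate treatment discontinuation from withdrawal of consent for data. That excuses silence, but the article is not silent: it states a rule without exception.

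These points reduce the size and certainty of the problem. They do not remove the rule or its effect on patients who could still have been observed.

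**Conclusion.** The point holds in a limited form. The stated rule risks avoidable, possibly outcome-related missing primary-outcome and safety data in a small unblinded trial analysed by intention to treat, and imputation may repair this only in part. The change is worth making, but the rule does not invalidate the design.

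A realistic scale is 0.05 to 0.15 cm per avoidable loss in an arm of 20, assuming pain 1 to 3 cm worse than imputed. The range 0.2 to 0.6 cm is an upper scenario and not an expectation: the planned 20% covers loss from all causes, and nothing in the documents says that it is all informative, avoidable or in one arm.

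A reader might also infer that the rule flatters surgery. The documents do not establish that, because losses of dissatisfied PT patients would act the other way. Nor do they show that the intention-to-treat analysis is defeated; that depends on how many withdraw and why.

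**What to change.** Amend the section on discontinuing or modifying allocated interventions so that data collection is decided separately from treatment. Neither withdrawal by the investigator for medical reasons nor a patient's decision to stop the allocated treatment should by itself end data collection.

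For these patients, continue the online VAS and other patient-reported questionnaires at 12/18 weeks, 26 weeks and 12 months. Continue adverse event recording over the window already planned (12 weeks for PT, 18 weeks for TTT). Stop only when the patient explicitly declines further data collection, and record that separately from the reason for withdrawal. Analyse everything collected by randomised arm.

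The cost is a short protocol and consent amendment and some extra contact with patients who have stopped treatment. Questionnaires are already online, and crossover patients are already followed in this way. The sample size does not change, and no clinical decision about treatment is touched.

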#### Strategies to improve adherence to interventions

To improve adherence, patients will receive the PT in text and with visual instructions on the Physitrack app if possible. They will also receive a weekly questionnaire to register the amount of exercising with the physiotherapist and at home, as well as their VAS score during the 12-week PT.

#### Relevant concomitant care permitted or prohibited during the trial

Patients are permitted to take any medication such as paracetamol or other prescribed painkillers. The use of other interventions, such as braces or insoles, is not restricted.

#### Provisions for post-trial care

Post-trial care will follow standard care, especially for the surgery group. Therefore, we do not expect post-trial harm from participation in this study. There are no specific provisions for post-trial care.

### Outcomes

#### Primary outcome

The main study parameter will be the between-group difference in activity-related knee pain at 12 weeks after PT in both groups, measured with the 10 cm VAS-scale. The point in time is different for the two groups, since there is a 6 week splint phase incorporated in the TTT group. Thus, knee pain will assessed at week 18 in the TTT group (6 weeks for the TTT and splint + 12 weeks of PT) and at week 12 in PT group. To compare both treatments as reliably as possible, we opted to not set this outcome measure further in time, due to the possibility for cross-over from the PT group to the TTT group. Furthermore, we expect that a plateau phase of pain will be reached within this period. The mean from the two VAS pain scores in week 12 (PT group) and 18 (TTT group) by the weekly questionnaire and outpatient visit will be used to account for variance in pain levels. Participants will assess the maximum pain they had felt during the previous 7 days when participating in activities of daily living such as ascending stairs, descending stairs and standing up from a sitting position. The 10-cm VAS is a valid and responsive tool for evaluating overall pain in patients with PFP [28]. A minimal clinically important difference (MCID) of 2 cm or 20% has been reported to reflect real changes in a patient’s symptoms [28].

#### Secondary outcomes

Secondary outcomes are between-group difference in: pain during the intervention (VAS); functional outcomes (Kujala score, IKDC), activity level (Tegner score), quality of life (EQ-5D-5 L), and functional ROM (DSDT) at 12/18 weeks follow-up, as well as the change over time from baseline to 12 months follow-up. Furthermore, this study will provide a global overview of the direct medical costs of surgery + PT compared to PT only treatment.

### VAS

In the TTT group, it could be possible that the trajectory of recovery might affect VAS pain scores at week 18 still. Therefore, a secondary outcome is the between-group difference in VAS pain score over time, which enables us to assess whether the VAS score at 12/18 weeks is stable or changes over time. This will be from baseline to 12 months follow-up, also including the VAS pain score in the weekly questionnaire during the PT.

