#### TTT and PT versus PT only

The study involves four outpatient visits (at inclusion/randomisation, 6 weeks after the start of the intervention, after 12 (PT group)/18 weeks (surgery + PT group), and after 26 weeks in both groups). A physical examination will take place at every outpatient visit, with the addition of the decline step-down test (DSDT) at baseline and 12/18 weeks after randomisation. Patients will complete online questionnaires at every outpatient visit and 12 months after randomisation.

After randomisation, patients will either have a TTT (treatment group) or start with the PT (control group). From 12 weeks, there will be the possibility to crossover from the PT group to surgery if the symptoms do not improve. The criteria for this are a persisting high level of pain and patient-reported lack of effect of the PT. In that case, surgery will be performed within 2 weeks. Participants will then follow the same protocol as the TTT group, including the PT programme, surveys, and physical measurements.

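### The between-group VAS difference over time cannot show whether TTT pain has settled by week 18, because crossover in the PT arm moves it independently of TTT pain

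*Protocol article*

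**What the plan says.** The Primary outcome section sets the comparison at week 18 for TTT and week 12 for PT. It gives two reasons for not going later. The first is that PT patients may cross over to surgery. The second is that "we expect that a plateau phase of pain will be reached within this period".

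The VAS section under the secondary outcomes then raises a doubt: "In the TTT group, it could be possible that the trajectory of recovery might affect VAS pain scores at week 18 still". Its answer is a secondary outcome, the "between-group difference in VAS pain score over time, which enables us to assess whether the VAS score at 12/18 weeks is stable". On the period covered it says: "This will be from baseline to 12 months follow-up, also including the VAS pain score in the weekly questionnaire during the PT".

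The section TTT and PT versus PT only opens the crossover route: "From 12 weeks, there will be the possibility to crossover from the PT group to surgery if the symptoms do not improve". Selection is on the outcome itself: "The criteria for this are a persisting high level of pain and patient-reported lack of effect of the PT". Surgery then follows within 2 weeks.

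The section on statistical methods makes intention to treat the principle for the primary analyses. The only other set named is a per-protocol set without crossovers, for comparison. The longitudinal model under Secondary endpoints lists patient, time and treatment group as fixed effects. It names no time-by-treatment term and no contrast within the TTT arm after week 18.

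**The concern.** The doubt concerns one arm: is TTT pain still changing after week 18? The quantity chosen to settle it is a difference between two arms. A difference reveals the movement of one arm only if the other stands still or its movement is known. Here the comparator changes in treatment from week 12 onward, and the patients who change are those with the most pain.

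Two wrong answers are possible. A stable TTT result can look like a fading benefit because crossovers improve after surgery. A TTT arm that is still improving, so that week 18 caught it early, can look stable because the PT arm improves alongside it. At stake is how the trial interprets its own primary time point.

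**Working it through.** **The plan's own figures.** The Sample size section assumes a PT mean of 6.2, an SD of 2.0, a relevant difference of 2, 80% power and two-sided alpha 0.05. The normal approximation gives n = 2 × (1.960 + 0.842)² × 2.0² / 2² = 15.7, so 16 per group, and 16 / 0.8 = 20 after 20% loss. Both stated figures are reproduced. They are not in dispute and only supply the scale: PT 6.2, TTT 6.2 − 2 = 4.2, gap 2.0.

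**Formula.** Let c be the share of the PT arm that crosses over, h the mean fall in pain of crossovers after the primary time point, and g the further fall in the TTT arm after week 18. PT patients who do not cross over are taken as unchanged. With crossovers kept in the PT arm:

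later gap (PT − TTT) = (6.2 − c·h) − (4.2 − g) = 2.0 + g − c·h

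The gap therefore changes by g − c·h. The question is about g alone. The protocol gives neither c nor h, so the values below are assumptions.

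**TTT flat (g = 0), crossovers gain 2 (h = 2).**

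| c | later gap | apparent change | true TTT change |
|---|---|---|---|
| 30% | 2.0 − 0.6 = 1.4 | −0.6 | 0 |
| 50% | 2.0 − 1.0 = 1.0 | −1.0 | 0 |
| 70% | 2.0 − 1.4 = 0.6 | −1.4 | 0 |

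**TTT falls a further 1.0 (g = 1), h = 2.** The gap should widen to 3.0. It becomes 2.6 at 20%, 2.2 at 40%, 2.0 at 50% and 1.8 at 60% crossover. At 50% it has not moved at all. If crossovers gain 3, exact cancellation comes at c = 1/3.

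**TTT flat, crossovers temporarily 1 worse (h = −1).** The gap widens by c, that is by 0.2 to 0.6 at 20 to 60% crossover. This matters for week 26. A patient who crosses over at week 12 and is operated on by week 14 is then about 12 weeks past surgery: 6 weeks of splint phase and 6 weeks into the 12-week physiotherapy programme. At that visit the gap could move either way.

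**The per-protocol set.** Dropping crossovers removes their post-surgical scores, but it drops patients chosen for high pain. If PT scores are normal with SD 2.0 and the highest share c crosses over, the remaining PT mean is 6.2 − 2.0·φ(k)/(1 − c), with k the (1 − c) normal quantile. This is 5.5 at 20%, 4.9 at 40% and 4.6 at 50%. The gap against 4.2 is then 1.3, 0.7 or 0.4 by selection alone. It is also still a difference between arms, so it still does not isolate g.

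**The contrast within the TTT arm.** TTT mean at week 18 minus TTT mean later equals g for every c and h. Its precision is t(0.975, n − 1) × 2.0 × √(2(1 − r)) / √n, assuming SD 2.0 and within-patient correlation r of 0.5 to 0.7. The 95% half-width is 1.07 to 0.83 cm with 16 patients and 0.94 to 0.73 cm with 20.

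**The case against.** **The wording can be read more widely.** The VAS section speaks of the score at 12/18 weeks, which covers both arms, and does not say that stability will be read from a constant gap alone. The objectives and secondary outcomes also mention longitudinal change, time enters the model as dummies, and spaghetti plots would show TTT patients still improving. The choice of post-model contrasts is commonly left to an analysis plan. This stands in part. But the article does more than leave the method open: it names the between-group difference as what makes the assessment possible. Read as covering both arms, a difference still shows the stability of neither. The plots are descriptive.

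**Crossover is acknowledged.** The Discussion concedes that comparisons beyond 12 weeks may be affected, and a per-protocol analysis is planned. Neither is tied to this check. The Discussion's reassurance that intention to treat limits the impact does not help here, since intention to treat is what carries crossovers' post-surgical scores into the PT arm.

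**The figures rest on assumed inputs.** This stands. The crossover shares, the gain after crossover and the constancy of other PT patients are all assumed, and exact cancellation needs g = c·h. The figures show what can happen, not how likely it is.

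**A reader might infer that the primary result is undermined.** The documents do not support that. The primary time point is set before crossover takes effect, its regression does not use later scores, and the plateau is only the second of two stated reasons for it. The check is a secondary outcome with no decision attached.

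**Conclusion.** The point holds as one about the quantity chosen. The late between-group VAS difference changes by g − c·h, whereas the stated doubt is about g. It can therefore mislead in both directions, and no other stated element of the plan repairs this. That conclusion needs only the crossover rule and the retention of crossovers in the PT arm.

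The size cannot be fixed from the protocol. With crossovers gaining 2 cm, other PT patients unchanged and TTT flat, the 2.0 cm gap falls to 1.4, 1.0 or 0.6 cm at 30, 50 or 70% crossover. The sample size and the primary analysis are not affected. The consequence is confined to the claim about whether the week-18 score is settled.

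It may be tempting to go further and declare a plateau whenever the confidence interval for the within-TTT change excludes 2 cm. The documents give 2 cm as a minimal clinically important difference, not as a margin for stability, and the rule would be too lenient. With the half-widths above, a true further fall of 0.6 cm gives upper limits of about 1.3 to 1.7 cm, and a fall of 1.0 cm about 1.7 to 2.1 cm. Most arms that are still improving would pass.

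**What to change.** In the VAS section and in Secondary endpoints:

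- Assess stability by the within-TTT-arm change in VAS from week 18 to week 26 and from week 18 to 12 months, each as an estimate with a 95% confidence interval, for example through time-by-treatment contrasts in the mixed model.
- Interpret the 12-month change in light of possible hardware removal after the 6-month visit, described in the section on tibial tubercle transfer. The week-26 change is less exposed to this.
- Report the late between-group difference separately, labelled as affected by crossover, and delete the claim that it shows whether the score is stable.
- Attach no plateau rule based on 2 cm. Either report the estimate and interval as they are, or let the sponsor prespecify a smaller margin with a justification.

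The cost is a few sentences. Questionnaires are already scheduled at 12/18 weeks, 26 weeks and 12 months, so no new data are needed. There are two small downsides. The within-arm change is not a randomised comparison, although the question is itself within-arm. And with 16 to 20 patients the interval is roughly ±0.7 to ±1.1 cm under the assumptions above, so it can exclude a large further change but not a small one.

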### Objectives

The primary objective of this study is to compare the between-group difference in knee pain over time for TTT followed by PT versus PT alone in patients aged 18–35 years with chronic PFP. We hypothesise that TTT combined with PT will result in a larger decrease in knee pain than PT alone.

Secondary objectives are to compare the between-group and longitudinal difference in change in (1) knee function, measured by validated Patient-Reported Outcome Measures (PROMs), (2) range of motion (ROM), (3) quality of life (QoL), (4) the functional limitations, and (5) the direct medical costs.

The results of this study can be used to develop and implement a better stepped-care treatment strategy for PFP and can be integrated into the national guideline for “anterior knee pain” [14].

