#### Physiotherapy (PT) programme

This will start as soon as possible in the PT group and after the splint phase in the TTT group; the PT group will not wear a splint. The PT will consist of three levels and will be supervised by a physiotherapist. According to predefined criteria, the physiotherapist decides whether a patient can step onto the next level within the PT. The PT consists of flexibility, neuromuscular coordination, and strength exercises for the quadriceps and hip muscles. The PT is developed by a team of experienced physiotherapists who are specialised in treating patients with PFP and based upon the most recent physiotherapeutic insights [8]. In addition to training, education about PFP is incorporated into the PT according to the most recent insights regarding pain mechanisms [26, 27]. Physiotherapists who participate as self-chosen treating health care professionals by patients will be requested to follow an instructional video developed by the REVITALISE study team. Additionally, the three levels of exercise of the PT programme are available on the Physitrack^®^ tool for both participating physiotherapists and patients with PFP to improve exercise adherence and support clinical decision-making. In total, there will be 12 sessions with the physiotherapist. In the first three weeks of the PT, patients visit the physiotherapist twice a week. This will occur once a week from week 3 to week 6. This will occur every other week from week 6 to week 12. However, the treating physiotherapist may increase or decrease the number of appointments if needed. Additionally, the physiotherapist may adjust the exercises, sets, repetitions, weight and duration of loading tailoring to the specific needs of the patient. Since it is our intention that the PT is adjusted to the needs of each individual patient, the exact adherence and deviations to the protocol will not be monitored specifically. However, if necessary, we will consult with the treating physiotherapist in case the patient is not compliant. Moreover, the physiotherapist will be contacted by the study coordinator at the end of the PT to inquire about possible feedback on the PT and patient adherence and progression. The PT is included in the supplementary material (Supplementary file 1), which contains more detailed information and instructions.

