#### Other study parameters

This study will include items strongly recommended by the International Patellofemoral Research Network (iPFRN) in the REPORT-PFP consensus statement [35]. These include demographics, such as age, biological sex, symptom duration, and unilateral/bilateral symptoms [35]. Furthermore, physical examination data, such as height and weight (and hence BMI) will be recorded. To evaluate the adherence to the PT, patients will also receive a weekly email during the PT asking how often they have visited the physiotherapist and how often they have executed the PT at home.

Any adverse events (AEs) will be monitored, as explained in the ‘Adverse event reporting and harms’ section. The rate of ROH after surgery will be registered as a separate outcome.

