#### Secondary endpoints

For the secondary parameters (functional outcomes on the Kujala and IKDC score, activity level on Tegner score, QoL on the EuroQol-5D-5 L score, and functional ROM on the DSDT score) at 12 weeks after the start of the PT (week 18 for TTT group), the between-group difference will be assessed using multivariable linear regression analysis in the same manner as the primary endpoint.

To assess the longitudinal clinical effectiveness of both groups, linear mixed models for repeated measures (MMRM) will be used for the secondary outcomes and activity-related knee pain on VAS score during the PT from baseline to 12 months follow-up. MMRMs take the correlation of multiple measurements over time within one patient into account. In the MMRM, these secondary outcomes will be analysed as dependent variables. To evaluate the effect at different time points, the fixed effects will be patient, time, and the treatment group (TTT versus PT only). Time will be included as dummy variable, with baseline as reference.

The main effects for treatment will be reported as difference in means with 95% confidence intervals (CI).

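### Weekly pain scores start only with physiotherapy, so the surgical arm's splint weeks are almost unmeasured in the secondary pain outcomes, and the time points mix three starting points

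*Protocol article*

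**What the plan says.** All references are to the protocol article.

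- **Aim.** The Objectives section sets out to "compare the between-group difference in knee pain over time for TTT followed by PT versus PT alone". Secondary outcomes lists, as a between-group difference, "pain during the intervention (VAS"), together with change from baseline to 12 months.
- **Longitudinal pain outcome.** The VAS section defines its span and data: "This will be from baseline to 12 months follow-up, also including the VAS pain score in the weekly questionnaire during the PT".
- **When weekly scores are taken.** Strategies to improve adherence to interventions describes a weekly questionnaire on exercise, "as well as their VAS score during the 12-week PT". Other study parameters gives the same window for the adherence items: "patients will also receive a weekly email during the PT".
- **When PT starts.** The Physiotherapy (PT) programme section states: "This will start as soon as possible in the PT group and after the splint phase in the TTT group". The splint phase is 4 to 6 weeks in the Tibial tubercle transfer (TTT) section and 6 weeks in Primary outcome. Surgery is targeted within 2 weeks of randomisation.
- **Visits.** TTT and PT versus PT only places the visits after inclusion at "6 weeks after the start of the intervention, after 12 (PT group)/18 weeks (surgery + PT group), and after 26 weeks in both groups". Questionnaires are completed at each visit and 12 months after randomisation.
- **Model.** Secondary endpoints specifies a repeated-measures mixed model: "Time will be included as dummy variable, with baseline as reference".

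**The concern.** Primary outcome counts surgery and splint as the first 6 of the TTT arm's 18 weeks, so they belong to that arm's treatment. A comparison of pain during the intervention should include them. As scheduled, it covers the whole intervention in the PT arm and mainly the rehabilitation part in the TTT arm. The gap follows from allocation, so it is differential by construction, and no later analysis plan can recover scores that were never collected.

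The second difficulty is the time variable. The 6-week visit is counted from the start of the intervention. The 12-month questionnaire and the 12/18-week step-down test are counted from randomisation. The weekly scores and the primary endpoint are counted from the start of PT. A single set of time levels cannot respect all three. If the levels are PT weeks, the surgical phase drops out of the comparison. If they are weeks since randomisation, the weekly series only partly overlap.

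What is at stake is the description of pain over the course of each strategy, a stated secondary outcome that patients and surgeons would read when weighing surgery.

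**Working it through.** **Inputs.** Weekly VAS in the 12 PT weeks; PT from week 0 in the PT arm and from the end of the splint phase (4 to 6 weeks, or 6) in the TTT arm; visits at 6, 12/18 and 26 weeks and a questionnaire at 12 months (week 52); 7-day recall (Primary outcome), so each score covers one week. Assumptions: surgery and PT-arm start at week 0, every form returned.

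**1. The plan's own figure.** 6 splint weeks + 12 PT weeks = 18 weeks. This reproduces the TTT time point. With a 4-week splint, PT week 12 falls at 4 + 12 = week 16.

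**2. Weeks covered by a scheduled score.**

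| | PT arm | TTT, 6-week splint | TTT, 4-week splint |
|---|---|---|---|
| Weekly series | 1–12 | 7–18 | 5–16 |
| Weeks 1–6 covered | 6 | 1 (week 6 visit) | 2 (weeks 5 and 6) |
| Early weeks uncovered | none | 1–5 | 1–4 |
| Weeks 1–18 covered | 12 | 13 | 13 |
| Weeks covered in both arms | – | 6–12, 26, 52 | 5–12, 26, 52 |

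The totals over 18 weeks are similar (12 and 13), but they fall in different weeks. With a 6-week splint the TTT arm lacks weeks 1–5 and the PT arm lacks weeks 13–18.

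**3. Alignment.**
- On the PT clock, the 6-week visit is PT week 6 in the PT arm but 6 − 6 = PT week 0 in the TTT arm (6 − 4 = 2 with a 4-week splint). The 26-week visit is PT week 26 against 26 − 6 = 20.
- On the randomisation clock, with surgery at week 0 and a 6-week splint, the weekly series overlap only in weeks 7–12.
- If surgery comes 2 weeks after randomisation and the splint lasts 6 weeks, PT begins after week 2 + 6 = 8. Weekly TTT scores then start in week 9, the overlap shrinks to weeks 9–12, and week 18 after randomisation is PT week 18 − 8 = 10.

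**4. Illustration of size.** The documents give no postoperative pain level, so an excess *e* in the TTT arm over the uncovered weeks is assumed. Unseen contribution to a mean over *W* weeks = (uncovered weeks × *e*) / *W*.

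- Five uncovered weeks, *W* = 18: 5 × 1 / 18 = 0.28 cm; 5 × 2 / 18 = 0.56 cm.
- Five uncovered weeks, *W* = 52: 5 × 1 / 52 = 0.10 cm; 5 × 2 / 52 = 0.19 cm.
- Four uncovered weeks, *W* = 18: 4 × 1 / 18 = 0.22 cm; 4 × 2 / 18 = 0.44 cm.

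For scale, the protocol's minimal clinically important difference is 2 cm. The protocol plans no 18-week mean; it serves here only to express the gap as one number.

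**The case against.** The strongest reply is that the VAS section gives a narrower reason for following pain over time: to see whether the 12/18-week score is stable, given that recovery might still affect week 18. That needs scores around and after that point, which are collected, and no splint-phase data. This is right for that aim. It does not cover the Objectives, or the separately listed outcome of pain during the intervention.

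Next, the VAS asks for maximum pain in daily activities such as stairs and rising from a chair. A patient in a splint and on crutches does these differently, so early scores may not measure quite the same thing. This stands as a caveat on interpretation.

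Third, coding of the time factor is commonly left to an analysis plan, and an article need not give it. That is fair for the coding alone. The mixed anchors and the collection window are stated in the article itself.

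Finally, PT patients may cross over to surgery from week 12, so PT-arm scores in weeks 13–18 may contain their own surgical weeks. Recruitment opened in October 2023, so patients already enrolled lack early scores. Both points stand and limit what the added data can show.

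**Conclusion.** The point holds as a gap in secondary outcomes. With a 6-week splint, postoperative weeks 1–5 have no scheduled score in the TTT arm (weeks 1–4 with a 4-week splint), while the PT arm is scored in every one of those weeks. This assumes surgery at week 0; a delay adds further unscored weeks after randomisation. The 0.28 to 0.56 cm illustration rests wholly on an assumed excess of 1 to 2 cm, and its direction depends on that assumption.

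A reader might infer more than the documents support:

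- *That the gap makes surgery look better, or hides its most painful phase.* The documents do not describe postoperative pain. Nor do they say that TTT patients have recovered when PT begins; the VAS section worries that recovery may still affect week 18.
- *That the arms have no common time points.* Baseline, week 6, week 26 and 12 months are nominally shared. The misalignment concerns the weekly and 12/18-week scores.
- *That the phase is wholly unmeasured.* The 6-week visit covers one week of it.
- *That the main result is at risk.* The primary endpoint compares scores at PT week 12, and the sample size of 16, inflated to 20, per group rests on that comparison. Neither uses splint-phase data.

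**What to change.** 1. Send the existing weekly VAS questionnaire from randomisation to week 18 in both arms. Where PT week 12 falls later than week 18, the PT questionnaires already planned simply continue.
2. In the longitudinal VAS model and plots, code time as weeks since randomisation in both arms. Keep PT-week alignment for the 12/18-week comparison.
3. Report splint-phase pain by randomised arm, with three notes: PT-arm scores after week 12 may include crossover surgery; the VAS refers to daily activities that splint and crutches limit; and patients already enrolled lack these scores.
4. If collection is not extended, rename the outcome as pain during PT and state that the surgical and splint phase is not covered.
5. Reconcile the two statements of splint length (Tibial tubercle transfer (TTT) and Primary outcome), because they determine when weekly scores begin and whether PT week 12 is week 18.

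Cost: about six extra emails per patient (roughly weeks 1–6 in the TTT arm and 13–18 in the PT arm) and a changed time coding, with no added visits or procedures. The drawbacks are a small added burden and incomplete early data for patients already enrolled.
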